### GA tools, questionnaires, and chemotherapy risk assessments

A list of GA tools and recommended intervention methods is shown in Table 1.

GA tools to be used include:

Lawton Instrumental Activities of Daily Living Scale,history of falls within the past 6 months,Charlson Comorbidity Index (CCI),Mini-Cog screening for cognitive impairment in older adults, and.Geriatric Depression Scale (GDS).

The number of medications used, body mass index, and social support will also be assessed as part of the GA.

Questionnaires to be employed include:

Patient Satisfaction Survey in HCCQ, and.European Organization for Research and Treatment of Cancers QLQ-C15-PAL.

Chemotherapy risk assessments to be performed are as follows:

Cancer and Aging Research Group score [4, 5], and.Geriatric 8 health status screening tool.Collect grade 3 or higher adverse events with Common Terminology Criteria for Adverse Events v5.0.

### Outcome

The primary outcome will be the change in the level of patient satisfaction according to the HCCQ questionnaire between the pre-treatment assessment and the post-treatment assessment conducted 3 months later.

## Sample size

For calculating the required number of subjects, first, the number needed for randomization of individual subjects will be calculated, followed by the number needed for cluster randomization. With reference to a report by Mohile et al. [6], it is predicted that the mean scores in the HCCQ Patient Satisfaction Survey before chemotherapy will be 23.3 and 22.2 in the intervention and non-intervention groups, respectively. Considering the common standard deviation for this variable to be 4.5, the two-sided α error to be 5 %, and the detection power to be 80 %, the required number of subjects is calculated to be 526.

Taking the required number of subjects for separate randomization to be *n*, the required number for cluster randomization to be *n’*, the cluster size to be *m*, and the intra-cluster correlation coefficient to be *ρ*, the formula is as follows:
$$n' = ([m - 1] \rho + 1) n$$

Using the above formula, taking *n* to be 526, *m* to be 15, and *ρ* to be 0.05 yields a value of 895 for *n’*, and a required number of clusters of 60; therefore, the number of study sites has been set at a minimum of 60. We assumed that 10 % of prospective participants would have at least one exclusion criterion, and thus the minimum number of participants required is 985.

In addition, in a previous study by our research group, it was found that, among lung cancer patients aged over 75 years, 97 % showed at least one vulnerability factor (unpublished data). Taking this into consideration, the sample size has been set at 1020. Eighty-one medical facilities (study sites) distributed throughout Japan have been selected for the study. We aim to enroll 15 participants per site.

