## Methods

### Study objective, design, and setting

The primary objective of the ENSURE-GA study is to evaluate the effect of an intervention based on a standardized GA on patient satisfaction with their treatment. This study will be a phase III comparative clinical trial with a cluster-randomized design and will be conducted in 81 medical facilities that have been selected based on the following four factors: (i) number of beds ( ≧ 200 beds or < 200 beds); (ii) whether or not designated as a cancer hospital by the Japanese Ministry of Health, Labor, and Welfare; (iii) region (divided into 6 regions, and these regions were evenly allocated with participating facilities from each region); and (iv) whether GA is usually included in medical treatment. Each facility will be randomly allocated in order of enrollment to the intervention or non-intervention group in a 1:1 ratio.

The primary endpoint will be the change in patient satisfaction according to the Health Care Communication Questionnaire (HCCQ) questionnaire between the GA and 3 months later. The secondary endpoints will be (i) the change in the quality of life; (ii) the treatment completion rate; (iii) the proportion of participants showing improvement by at least one grade in their Eastern Cooperative Oncology Group performance status (ECOG-PS); (iv) the relationship between the pre-chemotherapy risk assessment results and adverse events, evaluated separately for cytotoxic anticancer agents, molecular-targeted agents, and immune checkpoint inhibitors; and (v) the proportion of screened patients who had vulnerability factors in at least one of the GA tools and are enrolled in the study.

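### The sample size and its 80% power are worked out for HCCQ scores before chemotherapy, whereas the primary endpoint is the change in HCCQ to 3 months

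*Protocol article*

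**What the plan says.** The endpoint is defined twice, consistently. Under Study objective, design, and setting: "The primary endpoint will be the change in patient satisfaction according to the Health Care Communication Questionnaire (HCCQ) questionnaire between the GA and 3 months" afterwards. Under Outcome: "The primary outcome will be the change in the level of patient satisfaction according to the HCCQ questionnaire", measured from the pre-treatment assessment to the one 3 months later.

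The Sample size section uses a different variable. There "it is predicted that the mean scores in the HCCQ Patient Satisfaction Survey before chemotherapy will be 23.3 and 22.2" for the two groups, and the spread is attached to that same quantity: "Considering the common standard deviation for this variable to be 4.5". With a two-sided 5% level and 80% power, "the required number of subjects is calculated to be 526". A cluster size of 15 and an intra-cluster correlation of 0.05 raise this to 895 patients in 60 clusters. Allowances for exclusions and for patients without a vulnerability factor lead to 985 and then 1020. Eighty-one sites have been selected.

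The Methods paragraph of the Abstract places the first survey after the GA and before treatment starts. The Statistical analysis section names a mixed-effects model that allows for clustering and says no more about the model's terms.

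**The concern.** The effect of 1.1 points and the SD of 4.5 both describe a score at one time point, before treatment. The primary analysis compares a within-patient change, whose between-arm difference and SD are different quantities. The article gives neither, nor the correlation between the two surveys from which the SD could be obtained.

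The time point makes this more than a question of labelling. The score used for sizing falls at the starting point of the change. If the arms already differed by 1.1 before chemotherapy, as the sizing predicts, and that gap merely persisted to 3 months, the expected difference in change would be zero. The primary test would then reject only at its 5% level, although the sizing assumption had been met exactly.

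At stake is the only power justification given for 526, 895, 60 clusters and 1020, and with it how a null result could be read.

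**Working it through.** **Inputs from the Sample size section.** Means 23.3 and 22.2, so a difference of 1.1; SD 4.5; two-sided alpha 5%; power 80%; m = 15; ICC 0.05. The 1:1 allocation is from Study objective, design, and setting.

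**Step 1: reproduce the plan's figures.**
- n per arm = 2 × (1.96 + 0.8416)² × 4.5² / 1.1² = 262.7, so 263 per arm and 526 in total, as stated.
- Design effect = 1 + (15 − 1) × 0.05 = 1.70. 526 × 1.70 = 894.2, so 895. 894.2 / 15 = 59.6, so 60 clusters, as stated.

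The figures follow from the single-time score, and there is no arithmetic error.

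**Step 2: what the change endpoint would need.** With equal SDs at both times and correlation r between the surveys, SD of change = 4.5 × √(2(1 − r)). With 895 patients, power = Φ(d / (SD × √(4 × DE / 895)) − 1.96), where d is the between-arm difference in change and DE the design effect.

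The following are assumptions, not figures given for the change: d = 1.1; SD 4.5 at both times; no baseline adjustment; the ICC of 0.05 carried over to the change; and each r. Two design effects are shown. One is the plan's 1.70. The other spreads the 895 over the 81 selected sites: 895 / 81 = 11.05 per site, so DE = 1 + 10.05 × 0.05 = 1.50.

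| r | SD of change | Power, 15 per site | Power, 81 sites | d needed for 80% (15 per site) |
|---|---|---|---|---|
| 0.3 | 5.32 | 65.9% | 71.3% | 1.30 |
| 0.4 | 4.93 | 72.6% | 77.7% | 1.20 |
| 0.5 | 4.50 | 80.1% | 84.7% | 1.10 |
| 0.6 | 4.02 | 88.0% | 91.5% | 0.98 |
| 0.7 | 3.49 | 95.2% | 97.1% | 0.85 |

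The last column is (1.1 / 4.5) × SD of change. At 15 per site, 80% power needs only a ratio of difference to SD of about 0.244.

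**Step 3: sensitivity to the difference.** At r = 0.5 and 15 per site, the standard error is 4.5 × √(4 × 1.70 / 895) = 0.392.
- d = 0.8: Φ(0.8 / 0.392 − 1.96), about 53%.
- d = 0.55: about 29%.

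**The case against.** **The model may adjust for baseline.** The article says only that a mixed-effects model is used, and the covariates may properly be left to an analysis plan that is not shown. With baseline adjustment the residual SD is 4.5 × √(1 − r²), which is at most 4.5, so given a 1.1-point effect 526 would be enough at any r. This stands as far as the SD goes, and the table therefore describes one possible analysis. It does not rescue the effect size: 1.1 is still given for the time before chemotherapy, and nothing shown supports it as a difference at 3 months or in the change.

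**The ICC and cluster size may differ for the change.** This also stands. Stable differences between sites cancel in a change score, so its ICC need not be 0.05, and with 81 sites the average cluster is smaller than 15. Both points limit how much weight the table can bear.

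**The phrase may be a slip.** Possibly. The report that the figures come from is not at hand, so this cannot be settled here. If it is a slip, it still has to be corrected and the two inputs justified for the endpoint.

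**Stronger readings.** A reader might infer that the trial is underpowered, or that 80% power requires both r of at least 0.5 and a difference of 1.1. The documents support neither. Power exceeds 80% at higher correlations, and the last column of the table shows that a larger difference offsets a lower r and a smaller one suffices at a higher r.

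**Conclusion.** The point stands as a mismatch between the endpoint and the variable used for sizing. It is not an arithmetic error. The stated 80% power is shown for HCCQ scores before chemotherapy and is not shown for the 3-month change that the trial tests; no other section repairs this.

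The size of the consequence cannot be fixed from the article. Under the assumptions listed with the table, power for the change runs from about 66% to 95% for r between 0.3 and 0.7 at 15 per site, and from about 71% to 97% if the same 895 patients are spread over 81 sites. A smaller difference in change lowers it further. These figures show how far the stated power depends on quantities that are not given; they do not estimate the trial's true power.

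**What to change.** Restate the calculation for the variable that is tested. Give the expected between-arm difference in 3-month change, its SD (or the SD at each time and r), and the ICC of the change, each with its source. Then report the power that the planned 1020 patients at 81 sites provide. If the reference to the time before chemotherapy is a wording error, correct it and justify 1.1 and 4.5 for the endpoint as analysed.

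The cost is rewriting one paragraph. The restatement needs no extra enrolment. Its downside is that the stated power may become less favourable.

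Replacing the primary contrast with a 3-month score adjusted for an HCCQ taken before the GA report would be a larger change. The Abstract puts the first survey after the GA, and at intervention sites the report is displayed immediately. That route would therefore alter the survey timing as well as the primary contrast, and it would still need a justified 3-month difference.

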### Statistical analysis

A mixed-effects model will be used to perform intergroup comparisons taking intra-cluster correlation into consideration, and the 95 % confidence interval will be calculated. Statistical analyses are performed using the Statistical Analysis System, version 9.4 (SAS Institute Inc., NC, USA).

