**Methods:**

The study will be a phase III comparative clinical trial with a cluster-randomized design, and it will be conducted at 81 sites distributed throughout Japan. Approximately 1000 lung cancer patients aged ≥ 75 years will be enrolled in the study. All participants will undergo a standardized GA before starting treatment (using an iPad). At the intervention sites, the GA results and intervention method recommended on the basis of the GA results will be returned as an instant report to guide the physician’s choice of intervention. At the control sites, the physician will decide on interventions based on standard practice. All participants will complete a patient satisfaction survey before treatment initiation (after the GA) and 3 months later.

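### The primary endpoint is fixed as HCCQ change and the model as described names clustering only; a 3-month score adjusted for baseline and the four site factors would be more precise, and the factors' role in allocation needs stating

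*Protocol article*

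**What the plan says.** **Endpoint.** The Outcome section states: "The primary outcome will be the change in the level of patient satisfaction according to the HCCQ questionnaire", measured from the pre-treatment assessment to 3 months. The design section says the same.

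**Model.** The Statistical analysis section gives one sentence on the model: "A mixed-effects model will be used to perform intergroup comparisons taking intra-cluster correlation into consideration", with a 95% confidence interval. It neither lists covariates nor rules them out.

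**Site factors and allocation.** Under Study objective, design, and setting, the trial "will be conducted in 81 medical facilities that have been selected based on the following four factors": bed number, designation as a cancer hospital, region, and whether GA is part of usual care. On region it adds that "these regions were evenly allocated with participating facilities from each region". It then says: "Each facility will be randomly allocated in order of enrollment to the intervention or non-intervention group in a 1:1 ratio". No strata or minimisation factors are named there.

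**Sample size variable.** The calculation uses mean HCCQ scores that "before chemotherapy will be 23.3 and 22.2 in the intervention and non-intervention groups, respectively", with a common SD of 4.5. That is a score at one time, not a change.

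**Timing of the first survey.** The Abstract's Methods paragraph says: "All participants will complete a patient satisfaction survey before treatment initiation (after the GA) and 3 months later".

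**The concern.** An unadjusted change score subtracts the whole baseline value, whereas regression subtracts only the part that predicts the follow-up value. With equal SDs at the two times, the adjusted analysis has the smaller variance at every correlation below 1. Because the power calculation rests on the SD of a single-time score, an unadjusted change analysis could also fall short of the stated 80%.

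The four site factors act on whole sites, so they add to between-site variance, which is what the design effect pays for. Usual use of GA matters most, since it narrows the contrast between arms at the sites that have it. As listed, the factors exclude no hospital: every facility has either 200 or more beds or fewer, is designated or not, lies in one of six regions, and uses GA or does not. They read more like balancing factors than selection criteria, yet the allocation sentence does not use them. A reader cannot tell which role they had.

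**Working it through.** **Inputs from the Sample size section:** difference 23.3 − 22.2 = 1.1; SD 4.5; two-sided α 5%; power 80%; cluster size 15; intra-cluster correlation (ICC) 0.05. **Assumed:** r, the correlation between baseline and 3-month HCCQ, with equal SDs at both times.

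**1. The plan's own figures.** Per arm: 2 × (1.960 + 0.842)² × 4.5² / 1.1² = 262.7, so 263, or 526 in total. Design effect: 1 + 14 × 0.05 = 1.70. Then 526 × 1.70 = 894.2, so 895, and 894.2 / 15 = 59.6, so 60 clusters. All reproduce.

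**2. Change against adjusted score.** Change variance = 2 × 4.5² × (1 − r). Adjusted variance = 4.5² × (1 − r²). Their ratio, adjusted to change, is (1 + r)/2. Power = Φ(1.1/SE − 1.96), with SE = √(2 × variance × 1.70 / 447.5).

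Example at r = 0.3:
- Change: variance 28.35, SE 0.464, power Φ(0.41) = 66%.
- Adjusted: variance 18.43, SE 0.374, power Φ(0.98) = 84%.

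| r | SD change | SD adjusted | Variance ratio | Power, change | Power, adjusted | N for 80%, change | N for 80%, adjusted |
|---|---|---|---|---|---|---|---|
| 0.3 | 5.32 | 4.29 | 0.65 | 66% | 84% | 1252 | 817 |
| 0.4 | 4.93 | 4.12 | 0.70 | 73% | 86% | 1075 | 752 |
| 0.5 | 4.50 | 3.90 | 0.75 | 80% | 90% | 895 | 674 |
| 0.6 | 4.02 | 3.60 | 0.80 | 88% | 94% | 718 | 575 |
| 0.7 | 3.49 | 3.21 | 0.85 | 95% | 98% | 538 | 456 |

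The change SD equals 4.5 when 2(1 − r) = 1, that is r = 0.5. Under the same design effect, the stated 80% holds for unadjusted change only from about there upwards.

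**3. If stable site effects cancel.** Step 2 uses one design effect for both analyses, which is hard on the change score. Assume instead that site effects at the two times correlate 0.8. The between-site covariance is then 0.8 × 0.05 = 0.04 and, at r = 0.3, the within-site covariance is 0.26, both in units of 4.5².
- Change: 2(0.95 − 0.26) + 15 × 2(0.05 − 0.04) = 1.68, power 81%.
- Adjusted, with slope 0.26/0.95 = 0.274: about 1.36, power 88%.

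At r = 0.5 the same method gives 90% vs 94%. The gap is smaller but remains.

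**4. Site factors.** If they explain a share R² of the between-site variance, the design effect for a single-time score becomes 15 × 0.05 × (1 − R²) + 0.95. At R² = 0.25 this is 1.51 (power 84% at 895 patients); at R² = 0.5 it is 1.325 (89%). R² is assumed.

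**5. Chance imbalance without stratification** (hypergeometric, 40 vs 41 sites). The number of usual-GA sites is not given.

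| Usual-GA sites (assumed) | Arms differ by ≥ 10 points | Arms differ by ≥ 15 points |
|---|---|---|
| 4 | 5% | 0% |
| 8 | 15% | 3% |
| 16 | 28% | 10% |
| 40 | 38% | 18% |

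For scale, a factor present at half the sites has a 95% range of ±1.96 × √(0.25 × (1/40 + 1/41)) = ±22 points. If it moved HCCQ by an assumed 1 point, the shift would be about ±0.22 against the planned 1.1.

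**The case against.** A reader might infer that the plan commits to a raw change score and that the site factors enter neither the allocation nor the model. The document does not support that. It is silent on covariates, and an article commonly leaves the covariate list to the full protocol or SAP. A change endpoint does not imply an unadjusted model either: change analysed with baseline as a covariate gives the same treatment effect as the adjusted 3-month score. The region clause could be condensed wording for balanced allocation. These points stand, and they limit the finding to the analysis as described.

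The power gap also depends on r, which is not given, and shrinks at high r or when site effects are stable over time. That stands too, but the adjusted analysis is ahead in every case computed.

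A second tempting inference is that chance imbalance would bias the result. Under valid randomisation it does not bias the test or inflate type I error, and the random site effect carries it into the standard error. Its size is also uncertain: the Background says GA is not currently performed in Japanese practice, so usual-GA sites may be few.

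The most serious objection concerns baseline. The first HCCQ follows the GA, and intervention sites display the report immediately, so that score may already carry part of the effect. This argues more strongly against change than against adjustment. If the report has already moved baseline by δ, change removes all of δ, while regression removes about r × δ.

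**Conclusion.** The point holds as one of precision and clarity in the analysis as described. The plan's sample size arithmetic is correct on its inputs, but those inputs describe a single-time score. Unadjusted change matches the stated 80% only if r is about 0.5 or more under the same design effect. Baseline adjustment gains about 18 power points at r = 0.3, 10 at r = 0.5 and 2 at r = 0.7, or about 7 at r = 0.3 if site effects correlate 0.8 over time. These gains assume equal SDs and a baseline taken before the report is shown. The number of usual-GA sites and the effect of any site factor on HCCQ are unknown, so the 5% to 38% range for a gap of 10 points or more is only a guide. Nothing here shows that the trial's test is invalid.

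**What to change.** - **Primary model.** Analyse the 3-month HCCQ score in a mixed model with arm, baseline HCCQ and the four site factors (beds, cancer-hospital designation, region, usual GA) as fixed effects, and a random site intercept. Use the same model for all patients in both arms.
- **Baseline.** Take the first HCCQ before the report is shown. If that cannot be ensured, add a sensitivity analysis that leaves baseline out for both arms and keeps the site factors. Never drop baseline patient by patient according to report timing: only intervention sites display a report, so covariate use would then depend on arm.
- **Allocation.** State whether the four factors balanced the randomisation, and clarify the region clause. If they did, the model should carry them, because omitting stratification factors generally makes standard errors too large. If they did not, adjustment is the remaining protection.

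**Cost.** The model and allocation changes are wording only, and the site factors are already known. They use 5 degrees of freedom for six regions plus 3 for the binary factors, about 8 out of 81 sites. Moving the first survey ahead of the report is a change of procedure where sites do not already do so.

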## Discussion

GA for elderly cancer patients requires a multifaceted assessment, is complicated, and takes considerable time, and hence it has largely been avoided. For this study, detailed GA tools and intervention methods have been identified, and a simplified and standardized iPad system will be used to record the data. If the iPad GA system is shown to be feasible, it may encourage physicians to use this method of GA in general clinical practice and to base their interventions on the GA results. In 2019, Mohile et al. [6] reported that GA is effective for improving communication between patients and healthcare workers; however, only five phase III, comparative, clinical trials, including the ENSURE-GA study, have been conducted to determine the usefulness of GA, and there have been no trials that have evaluated interventions based on the results of a GA [1]. Japan has one of the highest levels of societal aging in the world, and GA is not currently used in standard practice to guide the treatment of older cancer patients.

In conclusion, the ENSURE-GA study will determine the usefulness of GA for individualizing the treatment of older patients with lung cancer. If the intervention is shown to be effective, it may lead to the increased use of GA and improved treatment of older cancer patients. The study has the potential to have a major impact not only on the management of lung cancer but also on the management of a wide range of cancer types. The results will also be used to prepare guidelines on treating older cancer patients and will establish a foundation for the development of a standardized geriatric oncology system.

